## Study Procedure risks

In applying to join the program, patients with severe depression/suicidality will be screened out and encouraged to see their GP. Patients will need to meet inclusion/exclusion criteria before joining the study. After satisfying these criteria, patients will be measured at pre-treatment, mid-treatment, post-treatment time points, with CaCCBT and CCBT groups measured at 3 month follow up and the waitlist control group measured immediately after completing the active treatment phase. If any responses to questionnaires at any of these timepoints indicate deterioration in wellbeing, this will be raised with the Chief Investigator, and or clinician to determine the best way of dealing with these difficulties. Additionally, regular team meetings (at least 3 times a week) will be conducted to monitor any difficulties patients may be having and ways of best dealing with these difficulties. Adverse events will be monitored by the investigators and reported to the Ethics Committees.

## Recruitment and screening

There are already over 1000 people on the waitlist for Virtual Clinic. The study will be described on the intake website, [www.virtualclinic.org.au](http://www.virtualclinic.org.au). People will read the information about the studies and elect to continue or not. If they choose to apply for the study they will complete an automated screening questionnaire to screen out participants with a history of schizophrenia/bi polar disorder, active suicidality, current substance use/dependence, or who do not meet the technical requirements of the study.

## Informed consent process

Only participants who have read the information about the studies, elected to complete the screening questionnaire, and meet selection criteria will be invited to participate. These participants will undergo a brief diagnostic interview, followed by further explanation of the study details, and an opportunity to ask questions about the study. A consent form will then be emailed to the participant. Informed consent will be taken as successfully returning the consent form. Additionally, informed consent will also be monitored during the study by the Chief Investigator, and each time a patient logs on to do a lesson, this will be taken as a sign of continued consent to participate.

## Enrolment procedure

Participants will be randomly allocated to Treatment Group 1, treatment Group 2, or the waitlist control group prior to completing the brief telephone interview.

## Randomization procedure

The website [www.random.org](http://www.random.org) will be used to determine a list of randomly generated numbers that correspond to a group (Group 1, 2 or waitlist control). Participants will be randomly allocated to one of these groups before completing the brief telephone interview.

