## Investigation plan

A CONSORT-R compliant, registered RCT of the intervention (CaCCBT) versus CCBT versus waitlist control group. This will demonstrate whether the benefit from the CaCCBT intervention is superior to natural remission and placebo response. Because of low adherence to CCBT we think that it is a proxy for a placebo treatment. As in any RCT accurate patient selection, good randomization, reliable and valid outcome measures, and low drop-out rates are critical. Analyses based on completers and on intention to treat will be performed.

There are already over 1000 people on the waitlist for Virtual Clinic. In addition, some media attention is expected to generate more publicity to attract people to the program. The study will be described on the intake website, [www.virtualclinic.org.au](http://www.virtualclinic.org.au). People will read the information about the studies and elect to continue or not. If they choose to apply for the study they will complete an automated screening questionnaire. Only people whose responses to the questions meet selection criteria and undergo a brief phone interview explaining the program will read the information sheet and return an electronic consent form and mail that to the investigators. This will trigger the phone interview in which the diagnosis will be confirmed using the Mini International Neuropsychiatric Interview Version 5.0.0 (Appendix A). Questions about the study will be answered and an offer of treatment made.

Patients will be randomly allocated to CaCCBT group (n=50), CCBT group (n=50), or the waitlist group (n=50). Randomization will be done via [www.random.org](http://www.random.org) (see appendix A).

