Upon beginning treatment, all participants will complete a set of diagnostic questionnaires. The questionnaires being administered in this study pre and post are the same as the study previously approved by St Vincent's Hospital Human Research Ethics Committee (09/021). However, one additional questionnaire has been added for assessing general anxiety (Depression, Anxiety, Stress Scale, DASS-21, Lovibond & Lovibond, 1995), three questionnaires for diagnosis specific measures of anxiety (Social Interaction Anxiety Scale/Social Phobia Scale Composite Short Form, SPSR, Peters et al, submitted,; Agoraphobic Cognitions Questionnaire, Chambless et al, 1984; Panic Disorder Severity Scale-Self Rating, PDSS-SR, Houck et al, 2002) and one questionnaires for associated variables (NEO-FFI, Costa & McCrae, 1992).

For the treatment groups, [name] and [name] will treat the participants. The treatment program is delivered via the website [www.virtualclinic.org.au](http://www.virtualclinic.org.au). The treatment program consists of 8 lessons conducted over a 10 week period, in which participants are encouraged to complete one lesson per week. The program is comprised of the following Lessons:

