# Blinding and unblinding

Study is not blinded.

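### Allocation is placed before the eligibility-deciding diagnostic interview and before the baseline questionnaires in an open trial, and other sections of the protocol contradict that order

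*Protocol*

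**What the plan says.** The timing of allocation is stated twice. Section 5.6, on enrolment, reads: "Participants will be randomly allocated to Treatment Group 1, treatment Group 2, or the waitlist control group prior to completing the brief telephone interview". Section 5.7 (Randomization procedure): "Participants will be randomly allocated to one of these groups before completing the brief telephone interview".

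Section 5.5 (Informed consent process) describes the interview and what follows it: "These participants will undergo a brief diagnostic interview, followed by further explanation of the study details", and then "A consent form will then be emailed to the participant". Section 4.1 (Inclusion criteria) requires the result of the telephone diagnostic interview to agree with the target diagnosis, so the interview decides eligibility.

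Section 5.2 (Investigation plan) gives a different account. A first short call explains the program, the applicant then returns the consent form, and "This will trigger the phone interview in which the diagnosis will be confirmed" with the MINI. An offer of treatment follows, and random allocation is mentioned only in the next paragraph. Section 5.3 (Study procedure risks) requires patients to satisfy the inclusion and exclusion criteria before they join.

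On the baseline, section 5.2 says: "Upon beginning treatment, all participants will complete a set of diagnostic questionnaires". The flow chart in 5.1 likewise lists randomisation before the pre-treatment assessment. Section 8.2 enters the baseline score as a covariate and promises both completer and intention-to-treat analyses. Section 7 says: "Study is not blinded". Appendix 11.4 has the allocation list generated before the study starts; nothing in the protocol says when an individual assignment is disclosed, or to whom.

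**The concern.** Randomisation makes the arms comparable at the moment of allocation. Any later step that can remove a person or alter a measurement is safe only if it cannot depend on the arm. Here two such steps follow allocation.

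The first is the diagnostic interview. If the interviewer knows the assignment, a borderline diagnosis can be judged in its light. An applicant who knows it can decline, most obviously on learning of the waitlist. The second primary hypothesis compares arms within primary-diagnosis groups, so the diagnosis confirmed at this interview also defines the groups being compared.

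The second is the baseline. It is self-reported and serves as the adjustment variable. If answers shift because the arm is known, the adjustment carries that shift into the estimated treatment effect.

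People lost between allocation and baseline would also lack the outcome baseline that the intention-to-treat analysis needs. Selection after allocation is hard to repair at the analysis stage.

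**Working it through.** **1. Order of steps.** Section 5.2 describes two calls and section 5.5 one, so the interview named in 5.6 and 5.7 can be matched to three candidates:

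| Interview meant in 5.6 and 5.7 | Allocation relative to diagnosis | Allocation relative to consent |
|---|---|---|
| The diagnostic interview of 5.5 | before | before |
| The explanatory call of 5.2 | before | before |
| The consent-triggered MINI call of 5.2 | before | not fixed; consent may come first |

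Allocation precedes confirmation of the diagnosis in every row. It precedes consent in two of the three. Allocation before the baseline questionnaires rests separately on 5.1 and 5.2. Against this stand section 5.3 and the narrative order of 5.2.

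**2. The plan's own figures.** This point disputes none of them. The protocol plans 50 per arm and between-group effects of 0.3 (CaCCBT against CCBT) and 0.6 (CaCCBT against waitlist). In SD units, with a two-sided 5% test assumed and no gain from the covariate, power = Φ(ES × √(n/2) − 1.96). For ES 0.6 and n = 50 this is Φ(0.6 × 5 − 1.96) = Φ(1.04) = 85%.

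**3. Illustrative bias.** The protocol gives no rate of loss after allocation, so these inputs are assumptions. Suppose a share d is lost from one arm only, and those lost differ by g SD from those kept. The mean of the whole arm is then (mean of those kept) + d × g, so the mean of those kept is off by d × g. With SE = √(1/50 + 1/(50(1 − d))), the type I error of an unadjusted two-sided 5% test is 1 − Φ(1.96 − dg/SE) + Φ(−1.96 − dg/SE).

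| d | g | bias (SD) | share of 0.3 | share of 0.6 | type I error |
|---|---|---|---|---|---|
| 10% | 0.5 | 0.05 | 17% | 8% | 5.7% |
| 10% | 1.0 | 0.10 | 33% | 17% | 7.8% |
| 20% | 0.5 | 0.10 | 33% | 17% | 7.6% |
| 20% | 1.0 | 0.20 | 67% | 33% | 15.6% |
| 30% | 0.5 | 0.15 | 50% | 25% | 10.5% |
| 30% | 1.0 | 0.30 | 100% | 50% | 27.5% |

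**4. Baseline.** The ANCOVA contrast is the post-treatment difference minus slope × the baseline difference. A baseline difference produced by knowledge of the arm therefore biases the contrast by slope × that difference. The protocol gives nothing from which to size it.

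**5. Precision, a separate and lesser matter.** If every arm loses 10, 20 or 30% and nobody is replaced, n is 45, 40 or 35 and power at ES 0.6 falls from 85% to 81, 77 or 71%. Ending with 50 per arm would need 50/(1 − d) = 56, 63 or 72 allocated. This is lost precision, not lost comparability.

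**The case against.** The protocol can be read more kindly. Section 5.3 requires eligibility before joining, section 1.2 speaks of recruiting people with the disorders and then allocating them, and the flow chart puts enrolment ahead of randomisation. The investigators may intend the usual order. That stands as evidence of a contradiction, but it does not cancel two explicit statements of the opposite order, one of them in the enrolment section itself. Section 5.2, for its part, only mentions allocation later and states no timing.

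Several stronger readings are tempting, and the documents do not support them:

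- **Allocation certainly precedes consent.** It does under 5.5 and under one reading of 5.2, but not necessarily if 5.6 and 5.7 mean the MINI call that consent triggers.
- **The most severe applicants are removed after allocation.** Sections 5.3 and 5.4 screen for schizophrenia and bipolar history, suicidality, substance use and severe depression at application. The protocol uses the MINI for the anxiety diagnoses. Later losses would mainly be unconfirmed diagnoses and refusals.
- **The arm is known at interview or baseline.** The absence of blinding makes this possible; no section says when the assignment is disclosed.
- **Those lost have no data.** They have completed the screening questionnaire. What they would lack is the outcome baseline. How the intention-to-treat set treats them may properly be left to an analysis plan and is no fault here.
- **The bias is about 0.19 SD.** That figure comes from removing exactly the most severe 10% of one arm: φ(1.28)/0.90 = 0.195. It is an unadjusted worst case.

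Baseline adjustment is also a real defence. Under a correct linear model, loss that depends only on baseline severity does not bias the adjusted contrast. It does not protect against loss related to motivation or expectation, or against a baseline that is itself shifted. Finally, with over 1000 people waiting, lost participants could be replaced. That restores numbers but does not undo selection.

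**Conclusion.** The concern holds. Confidence is high that the protocol, as worded, allocates before the diagnostic interview that decides eligibility and before the baseline questionnaires, and that this contradicts section 5.3 and the narrative of 5.2. Confidence is moderate that allocation precedes consent and that baseline answers would be affected, because the first depends on which call is meant and the second on when the arm is disclosed.

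The conclusion is that the plan permits exclusions, refusals and baseline answers to be influenced by the arm; the documents do not show that they would be. The illustrative unadjusted bias of 0.05 to 0.30 SD rests wholly on assumed one-arm losses of 10–30% and differences of 0.5–1.0 SD. At the low end it is minor. At the high end it equals the whole expected CaCCBT–CCBT difference. Baseline adjustment would remove part of it. The point does not depend on these figures: the order of steps should be settled before enrolment.

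**What to change.** Reconcile sections 5.1, 5.2, 5.5, 5.6 and 5.7 into one sequence:

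1. automated screening questionnaire;
2. information and consent;
3. MINI interview confirming eligibility and primary diagnosis;
4. online pre-treatment questionnaires;
5. allocation from the pre-generated list, with each assignment released only after eligibility is recorded.

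Count the 150 at step 5. Use one name for each telephone call throughout, so that the explanatory call and the diagnostic interview cannot be confused.

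The cost is a short amendment and a re-ordering of online and telephone steps that already exist. No new procedure or staff is needed, and the sample size is unchanged. The one small downside is that applicants learn their arm slightly later.

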# Safety

## Adverse event reporting

There are no known risks associated with this treatment. Adverse events will include events that prohibit study participants from accessing the Program. Regular team meetings (at least 3 times a week) will be conducted to monitor any difficulties patients may be having and ways of best dealing with these difficulties. Adverse events will be reported to the Ethics Committee.

## Serious adverse event reporting

There are no known risks associated with this treatment. Serious adverse events will be those indicating deterioration in wellbeing as per questionnaire responses at the time points throughout the program. Regular team meetings (at least 3 times a week) will be conducted to monitor any difficulties patients may be having and ways of best dealing with these difficulties. Serious adverse events will be reported to the Ethics Committee.

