**Lesson Eight:**

- **Revise the skills you have learnt.**
- **Make a plan for staying well in the future.**

Participants in the CaCCBT group will receive regular email contact with their clinician, and will be encouraged to carry out homework activities.The patients in the CCBT groups will have same access to the lessons, and homework activities as the CaCCBT groups. Unlike the CaCCBT groups, the CCBT groups will have no clinician contact over the 10 week period, but will receive weekly telephone reminders from administrative staff. The waitlist group will not receive any treatment during this period.

After the treatment group has finished the program, all participants will complete a third set of diagnostic questionnaires. The waitlist group, and any CCBT participants wishing to complete the program with clinician contact, will be offered additional treatment after this.

Effectiveness of the CaCCBT program for anxiety will be measured by comparing waitlist and CCCBT and CaCCBT groups on their pre- and post- treatment scores. Long-term follow up data will compare the CaCCBT and CCBT groups at 3 month follow up.

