## Early termination

If a patient wishes to withdraw from the study once it has started, he or she can do so at any time without having to give a reason. Upon early withdrawal, all participants will be provided with encouragement to access additional services via their GP. Additionally, all participants will be given the opportunity to provide feedback about their current symptoms. If participants withdrawing from the program do report a deterioration of their symptoms, they will be contacted by the Chief Investigator to discuss access to additional services. If participants do not choose to provide feedback about their symptoms, but the investigators do have concerns about the participant’s condition, we do have consent from all participants to contact their GP. This process will be supervised by the Chief Investigator.

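### Section 6.2 defines a serious adverse event only by worsening on scheduled questionnaires, with no outcome-based criterion and no threshold, and the one adverse event criterion named in 6.1 cannot occur on the waitlist

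*Protocol*

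**What the plan says.** Four parts of the protocol bear on this point.

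- **6.2, Serious adverse event reporting:** "Serious adverse events will be those indicating deterioration in wellbeing as per questionnaire responses at the time points throughout the program". No other criterion is given.
- **6.1, Adverse event reporting:** "Adverse events will include events that prohibit study participants from accessing the Program". This is the only criterion named, and the verb leaves the list open.
- **5.3, Study procedure risks:** "patients will be measured at pre-treatment, mid-treatment, post-treatment time points, with CaCCBT and CCBT groups measured at 3 month follow up". On deterioration it adds: "If any responses to questionnaires at any of these timepoints indicate deterioration in wellbeing, this will be raised with the Chief Investigator". It does not call such a response a serious adverse event and gives no size of worsening.
- **Early termination (6.5 in the contents list):** "If participants withdrawing from the program do report a deterioration of their symptoms, they will be contacted by the Chief Investigator". It does not say whether this is an adverse event, a serious one or neither.

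The arms differ in what they receive during the 10 weeks (5.2, Investigation plan). For CaCCBT: "Participants in the CaCCBT group will receive regular email contact with their clinician". The CCBT arm "will have no clinician contact over the 10 week period, but will receive weekly telephone reminders from administrative staff". For the third arm: "The waitlist group will not receive any treatment during this period".

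Both 6.1 and 6.2 send their events to the Ethics Committee, and both provide for team meetings at least three times a week.

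**The concern.** Seriousness normally describes what happened to the participant. Section 6.2 makes it a property of a questionnaire response at a fixed time, and this can go wrong in two directions.

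- **Too narrow.** A grave event that no completed questionnaire records falls outside the definition. The participants most likely to be missed are those who stop responding. The trial is delivered remotely and excludes severe depression and current suicidality at entry, so the protocol itself recognises the risk.
- **Too wide.** With no instrument and no size of worsening, nothing in 6.2 prevents ordinary score fluctuation from being labelled serious.

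Section 6.1 does not fill the gap. A computer fault meets its named criterion. Self-harm that leaves Program access intact is not named in either section, and adding it as an adverse event under 6.1 would still not make it serious under 6.2.

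At stake are the correct labelling of serious events in reports to the Ethics Committee and the meaning of any table of harms by arm.

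**Working it through.** **1. Which events each rule catches, read as written**

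| Event | 6.1 named criterion | 6.2 rule |
|---|---|---|
| Hospitalisation between time points, not reflected in a questionnaire | Only if it blocks access (the open list may admit it otherwise) | Not serious |
| Self-harm in a participant who has stopped answering | Same | Not serious |
| Death before the next assessment | Same | Not serious |
| Loss of internet access | Yes | Not serious |
| Small score rise at mid-treatment | No | Can be serious |

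**2. Which comparisons between arms are possible**

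- *Named criterion in 6.1.* The waitlist has no Program to access in the controlled period, so its count is zero by construction. Comparison with the waitlist is not possible. CaCCBT and CCBT can be compared.
- *Questionnaire deterioration, pre to post.* Section 5.3 measures patients at pre, mid and post, and the flow chart in 5.1 gives the waitlist corresponding time points. All three arms can be compared once an instrument and a size are fixed.
- *Questionnaire deterioration at 3 months.* Only the two active arms are measured then. There is no waitlist comparison.
- *Events outside the questionnaires.* CaCCBT has clinician email, CCBT has weekly administrative calls, and the waitlist has no treatment contact. Detection may differ between arms unless all are asked the same question.

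**3. How much the missing threshold matters (illustration only)**

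The protocol gives no safety rate or threshold to reproduce.

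Inputs from 8.1, Sample Size Calculation:
- CaCCBT pre-post effect size: 1.0
- CCBT: 1.0 − 0.3 = 0.7
- Waitlist: 1.0 − 0.6 = 0.4

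Arm size is 50 (3.3). The subtraction assumes that all three figures are in the same SD units.

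Assumptions not in the documents: one scale, normal change scores, equal SDs before and after, and a pre-post correlation r between 0.5 and 0.8.

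SD of change: s = √(2(1 − r)), which is 1.000 at r = 0.5, 0.775 at r = 0.7 and 0.632 at r = 0.8.

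Any worse score: P = Φ(−ES/s). For example, for the waitlist at r = 0.5, Φ(−0.4/1.000) = 0.345. For CaCCBT at r = 0.8, Φ(−1.0/0.632) = 0.057.

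| r | CaCCBT | CCBT | Waitlist |
|---|---|---|---|
| 0.5 | 15.9% (7.9 of 50) | 24.2% (12.1) | 34.5% (17.2) |
| 0.7 | 9.8% (4.9) | 18.3% (9.2) | 30.3% (15.1) |
| 0.8 | 5.7% (2.8) | 13.4% (6.7) | 26.4% (13.2) |

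The waitlist rate is 34.5/15.9 = 2.2 to 26.4/5.7 = 4.6 times the CaCCBT rate. This comes entirely from the assumed treatment effect; no harm was put into the calculation.

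Reliable-change cut-off (worsening of more than 1.96 × s): P = Φ(−ES/s − 1.96). The largest value is for the waitlist at r = 0.5: Φ(−2.36) = 0.9%. The smallest is for CaCCBT at r = 0.8, about 0.02%. Every arm is below 1% on one scale.

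**The case against.** The protocol is more protective than 6.2 alone suggests. Section 6.1 says what adverse events include and does not close the list, so an investigator may record a hospitalisation or self-harm event in any arm. Adverse events of either class go to the Ethics Committee. Section 5.3 passes questionnaire deterioration to the Chief Investigator or clinician, which introduces judgement. Early termination provides for symptom feedback, follow-up by the Chief Investigator and consent to contact the general practitioner. A numerical cut-off could also sit in a document that is not shown.

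Most of this stands, and it limits what may be claimed. Three stronger readings are tempting but unsupported.

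- *The adverse event rule turns solely on Program access.* It does not; access is only the one criterion named.
- *Harms cannot be compared between arms at all.* All three arms have questionnaires at pre, mid and post, so the 6.2 rule is not arm-dependent over the controlled period.
- *Nearly everyone would have a serious event.* A simulation counting any worsening on any of nine listed symptom or disability scales gives 82-96% with no true change. It needs a reading that 6.2 does not state, a single assumed test-retest value of 0.7, assumed correlations of 0.3 to 0.7 between changes on different scales, and no improvement even on the waitlist, contrary to what 8.1 implies. It is not evidence of what would happen.

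What the objection does not answer is the wording of 6.2. It says what serious adverse events will be. None of the monitoring provisions classifies an event as serious, and an event admitted under 6.1 remains non-serious under 6.2. This is a stated rule that is wrong, not a detail left for later.

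**Conclusion.** The point holds as a defect of definition. Section 6.2 lacks any outcome-based seriousness criterion, any instrument and any size of worsening. This conclusion rests on the text alone and needs no numerical assumption. The likely consequence is mislabelling. The care and reporting provisions elsewhere mean that one cannot infer that grave events would go unnoticed or unreported altogether.

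The limits on comparison are specific: the named criterion in 6.1 against the waitlist, and questionnaire deterioration against the waitlist at 3 months.

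The size is illustrative. On one scale, with r assumed between 0.5 and 0.8, counting any worse score gives 6-16% in CaCCBT, 13-24% in CCBT and 26-34% on the waitlist, against below 1% in every arm with a reliable-change cut-off. The exact rates depend on the assumed correlation, on normality and on applying the anxiety effect sizes of 8.1 to the scale in question. Across the whole assumed range, the count is governed by the unstated threshold, and without one it largely restates the efficacy result.

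**What to change.** 1. In 6.1, define an adverse event as any untoward event in any arm, whether or not it affects Program access.
2. In 6.2, define a serious adverse event by its outcome (for example death, a life-threatening event, hospitalisation or self-harm), learned from any source and applied identically in all three arms.
3. Report questionnaire deterioration separately by arm as a monitored outcome. The investigators should fix the instrument and the size of worsening in advance. State that comparison with the waitlist is limited to the controlled period.
4. Add one event question to the existing assessments, worded the same in every arm.
5. Reconcile 5.3, 6.1, 6.2 and Early termination so that each report of deterioration has one classification.

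The cost is protocol wording and slightly more data entry from the added question. No visit, sample size or treatment changes.
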